## 2 INTRODUCTION

### 2.1 Sickle Cell Disease and Pulmonary Hypertension

Sickle cell disease (SCD) occurs in individuals who are homozygous for a single nucleotide substitution in the  $\beta$ -globin gene that ultimately renders their hemoglobin (HbS) much less soluble than normal hemoglobin (HbA) when deoxygenated. This insolubility causes aggregation (or polymerization) of HbS inside sickle erythrocytes as they traverse the microcirculation. The severity of sickle cell anemia has been described by models that emphasize either the intracellular kinetics of polymer formation and cell sickling or the extent of polymerization and cell rigidity at the reduced oxygen saturation values of various tissues and organs. The pathogenesis of sickle cell anemia is also thought to be affected by adhesion of the sickle erythrocytes to the microvascular endothelium. Increased expression of adhesion molecules on erythrocytes ( $\alpha 4\beta 1$ , CD36) and endothelial cells (VCAM-1, CD36), interaction with leukocytes, increased levels of circulating inflammatory cytokines, enhanced microvascular thrombosis, and endothelial damage are all thought to contribute to obstruction of the arterioles by polymer-containing sickle erythrocytes. Factors that increase the intracellular concentration of hemoglobin (red blood cell dehydration), increase time spent in the microcirculation (increased expression of adhesion molecules endothelial VCAM-1 and erythrocyte  $\alpha 4\beta 1$ ), or increase deoxygenation of hemoglobin, all contribute to increased HbS polymerization. Other sickle cell syndromes, include sickle-hemoglobin C (HbSC), sickle-hemoglobin D (HbSD), and sickle- $\beta^{0/+}$  thalassemia (HbS $\beta^{thal}$ ), vary in severity as compared to sickle cell anemia (HbSS), but sickle hemoglobin polymerization, chronic vascular injury and organ damage can occur.

Pulmonary hypertension, a disorder characterized by an elevated pulmonary artery pressure (PAP) and pulmonary vascular resistance (PVR), is an increasingly recognized complication of sickle cell anemia. Pulmonary hypertension has been defined by the 1981 NHLBI/NIH national registry as a mean pulmonary artery pressure (MPAP)  $\geq 25$  mm Hg at rest or  $\geq 30$  mm Hg with exercise. Echocardiographic studies performed at tertiary care sickle cell centers have reported that 10-30% of screened patients have pulmonary hypertension (MPAP  $\geq 25$  mm Hg). Furthermore, sickle cell patients with pulmonary hypertension have significantly increased mortality rate compared with patients without pulmonary hypertension. Sutton and colleagues reported a 40% mortality rate at 22 months with an odds ratio for death of 7.86 (2.63-23.4). Powars and colleagues reported a mean 2.5 year survival in sickle cell patients with chronic lung disease with pulmonary hypertension. Data presented at the 1999 American Thoracic Society by investigators at Wayne State University revealed a 30% prevalence of pulmonary hypertension in their sickle cell clinic population and a 30% two-month mortality rate. Castro and colleagues reported a 50% two year mortality rate in patients with sickle cell disease with pulmonary hypertension confirmed by right heart catheterization (RHC). It is clear that this disease, similar to idiopathic PAH (formerly primary pulmonary hypertension) and pulmonary hypertension associated with other conditions, e.g. scleroderma and HIV, carries an unacceptably high morbidity and mortality rate. The variability in 6 to 12 month prognoses is likely attributable to the variability in the PH in the patients studied.

These data are consistent with the results of an NIH pulmonary hypertension screening study. 195 adult patients with sickle cell disease were recruited from the greater Washington, DC region. All patients were screened with transthoracic echocardiograms and the tricuspid regurgitant jet velocity (TRV) was used to estimate the pulmonary artery systolic pressure. Pulmonary hypertension was prospectively defined by a TRV  $\geq$  2.5 m/s and moderate-to-severe PH defined by a TRV  $\geq$  3.0 m/s. Right heart catheterization was performed in consenting patients with TRV  $\geq$  2.8 m/s. This study revealed that 32% of patients with SCD had elevated pulmonary artery systolic pressure (TRV  $\geq$  2.5 m/s) and 9% had at least moderately elevated pressures (TRV  $\geq$  3.0 m/s). Multiple logistic regression analysis identified a history of renal or cardiovascular complications, increased systemic systolic blood pressure, markers of hemolysis (LDH), elevated alkaline phosphatase, and low transferrin levels as independent predictors of PH. Most importantly, TRV of at least 2.5 m/s, as compared to a velocity  $<$  2.5 m/s, was associated with an increased risk of death (RR 10.1; 95% CI, 2.2-47;  $P < 0.001$ ) and remained so after adjustment for other possible risk-factors in proportional hazards regression analysis. The 18 month mortality approached 20% for patients with a TRV  $\geq$  2.5 m/s. In another recent prospective study of 60 patients systematically sampled at a comprehensive sickle cell treatment center, the prevalence of PH (defined by an age and body-mass index adjusted nomogram) was 30 %. Further updated follow-up data from our cohort continues to demonstrate that PH is a strong independent risk factor for mortality with 45-month mortality rate of approximately 40 %. From Cox regression analysis the estimated risk ratio of death, relative to patients with TRV  $<$  2.5 m/s, was 4.4 (95% CI 1.6 to 12.2;  $P < 0.001$ ) for patients with TRV 2.5 to  $<$  3.0 m/s and 10.6 (95% CI 3.3 to 33.6;  $P < 0.001$ ) for patients with TRV  $>$  3.0 m/s. In addition, a study by De Castro and colleagues presented at the meeting of the American Society of Hematology reported a similar prevalence of PH and a remarkably similar 17% mortality rate for patients with PH over 2 years compared with approximately 2% for subjects without pulmonary hypertension. Ataga and colleagues have also shown a 10% mortality rate for patients with PH over 26 months in comparison to 1% in those patients without PH. Taken together, the retrospective and prospective studies strongly support the contention that PH is the greatest risk factor facing the aging population of patients with sickle cell disease and likely patients with other chronic hemolytic disorders.

Clearly, therapeutic trials targeting pulmonary hypertension in this high risk population are indicated.

## **2.2 Decreased NO Bioavailability in Hemolytic Disorders Provide Rationale for NO Based Therapies of Pulmonary Hypertension**

As a result of hemolysis, hemoglobin is released into plasma where it reacts with and destroys nitric oxide (NO), resulting in abnormally high NO consumption. Consequently, smooth muscle guanylyl cyclase is not activated and vasodilation is inhibited. Plasma from patients with SCD contains cell-free ferrous hemoglobin, which stoichiometrically consumes micromolar quantities of NO and abrogates forearm blood flow responses to NO donor infusions, and that hemoglobin oxidation by NO inhalation restores NO bioavailability. As such, plasma hemoglobin and oxygen free radical-mediated consumption of NO produces a state of resistance to NO in patients with sickle cell

disease. NO destruction by hemoglobin can also cause further impairment in vascular endothelial function via transcription derepression of adhesion molecules, including VCAM-1 and E-selectin, and vasoconstrictor/growth factors such as endothelin-1. In addition to hemoglobin decompartmentalization, hemolysis releases erythrocyte arginase, which converts L-arginine, the substrate for NO synthesis, to ornithine. Consistent with this observation, in patients with sickle cell disease, the arginine-to-ornithine ratio decreases significantly as pulmonary pressures increase and the patients with low ratios have the highest prospective mortality.

These alterations in NO bioavailability are likely to be involved in the pathogenesis of the secondary PH associated with SCD and other chronic hemolytic disorders. As such, therapeutic interventions that enhance NO effects or act as NO donors are of potential benefit and may alter the progression of the disorder. The sub-population of patients with SCD who have PH suffers the highest morbidity and mortality and is most likely to respond to these therapies.

Elevation in lactate dehydrogenase (LDH) is significantly associated with evidence of chronic hemolysis, including low levels of hemoglobin and haptoglobin, high levels of reticulocytes, bilirubin, plasma hemoglobin, and aspartate aminotransferase (AST). Elevated LDH levels also closely correlates with accelerated NO consumption by plasma, impaired vasodilatory response to NO donors, and is identified in patients with a syndrome of hemolysis-associated NO resistance, endothelial dysfunction and end-organ vasculopathy. This association has been confirmed in a longitudinal study of pulmonary hypertension in sickle cell disease patients. It has been suggested that LDH may be a simple but important biomarker for the clinical phenotype of pulmonary hypertension induced by chronic hemolysis.

### **2.3 Sildenafil Therapy in Hemolysis Associated Pulmonary Hypertension**

Endothelial NO activates the enzyme guanylate cyclase, which results in increased levels of cyclic guanosine monophosphate (cGMP), producing smooth muscle relaxation. Sildenafil has no direct relaxant effect, but enhances the effect of NO by inhibiting phosphodiesterase type 5 (PDE5), which is responsible for degradation of cGMP. Studies *in vitro* have shown that sildenafil is selective for PDE5. Its effect is more potent on PDE5 than on other known phosphodiesterases (>80-fold for PDE1, >1,000-fold for PDE2, PDE3, and PDE4).

In addition to human corpus cavernosum smooth muscle, PDE5 is also found in lower concentrations in other tissues including platelets, vascular and visceral smooth muscle, and skeletal muscle. The inhibition of PDE5 in these tissues by sildenafil may be the basis for the enhanced platelet anti-aggregatory activity of NO observed *in vitro*, an inhibition of platelet thrombus formation *in vivo* and peripheral arterial-venous dilatation *in vivo*. Recent studies now suggest that PDE5 is also present in greater abundance in the pulmonary vasculature. Sildenafil has thus been found to promote relatively selective pulmonary vasodilation in different subgroups of patients with pulmonary hypertension and is being utilized as an alternative therapeutic agent.

Acute administration of a single oral dose of sildenafil (50-100 mg) causes a significant decrease in MPAP, PVR with minimal or no effects on mean systemic arterial pressure. The effect peaks at 60 minutes and lasts as long as 4 hours. The magnitude of the effect in the pulmonary circulation is comparable to that of inhaled NO, iloprost and epoprostenol.

Case series have also documented a favorable effect of chronic sildenafil administration in patients with PH. Ghofrani et al treated 12 patients with inoperable chronic thromboembolic disease and PH. After 6 months of sildenafil therapy (50 mg three times/day) MPAP decreased from 53 to 45 mmHg ( $P = 0.03$ ) and 6MW distance increased from 312 to 366 m ( $P = 0.02$ ). Three months of sildenafil therapy added to standard of care was also associated with improvements in functional class, walking distance, PAP and right ventricular mass in five individuals with PH. In another group of 14 patients with PH failing iloprost therapy, the addition of sildenafil for up to 12 months was also associated with improvements in pulmonary hemodynamics and exercise capacity. The cumulative published experience from case series involving more than two patients is summarized in Table 1. A recently completed phase III study of sildenafil for PH confirmed these observations. In this trial 277 patients were randomized to receive placebo or sildenafil 20mg, 40mg or 80mg three times daily. All three sildenafil treatment groups demonstrated a significant improvement in exercise capacity when compared to placebo with placebo corrected effects on 6MW distance ranging from 45 to 50 m, but without a dose related response. Sildenafil treatment significantly decreased MPAP and PVR and increased cardiac output and mixed venous oxygen saturation; these hemodynamic responses were maximal at 80 mg three times a day. None of the men enrolled in these trials experienced priapism or unwanted erections.

Over the last four years we have treated 22 patients with SCD and PH with sildenafil under protocols 03-CC-0127 and 01-H-0223, for a combined total exposure time of 44 patient years. These experiences suggest that sildenafil is well tolerated in this population (see section 12.3.2) and effectively lowers PAPs and increases exercise capacity (Figure 1). None of the male patients experienced severe sustained priapism. While the observed effects are comparable to inhaled NO gas, the oral modality of sildenafil therapy offers substantial advantages. Based on these data, we hypothesize that chronic sildenafil therapy in patients with PH associated with SCD will result in improvements in exercise capacity and pulmonary hemodynamics.

**Table 1. Summary of Relevant Literature**

| Reference         | Number of Patients | Dose              | Duration | Main Results                                                          |
|--------------------------|---------------------------|--------------------------|-----------------|------------------------------------------------------------------------------|
| Lepore      | 9                         | 50 mg X1                 | Single dose     | Significant decrease in MPAP                                                 |
| Michelakis  | 13                        | 75 mg X1                 | Single dose     | Significant 27% decrease in MPAP                                             |
| Ghofrani    | 8                         | 50 mg                    | Single dose     | Significant 32.5 % decrease in PVR index                                     |
| Michelakis  | 5                         | 50 mg TID                | 3 months        | Significant improvement in NYHA functional class, 6MW distance, MPAP and PVR |
| Ghofrani    | 14                        | 25 mg TID- 50 mg TID     | 9-12 months     | Significant improvement in NYHA functional class, 6MW distance, MPAP and PVR |
| Ghofrani    | 12                        | 50 mg TID                | 6 months        | Significant improvement in 6MW distance, MPAP and PVR                        |
| Galie       | 278                       | 20mg, 40 mg or 60 mg TID | 12 weeks        | Significant improvement in MPAP, oxygen saturation and exercise capacity     |

**Figure 1. Effects of sildenafil on (A) pulmonary pressures and (B) functional capacity**

**Subtitle: As measured by six minute walk distance, in patients with pulmonary hypertension and sickle cell disease**

[figure not shown]

A)

[figure not shown]

B)

## **2.4 Genetic Epidemiology and Candidate Gene Modifiers in Sickle Cell Hemolysis Associated Pulmonary Hypertension**

Clinical risk factors only account for 40% ( $R^2=0.40$ ) of the variability associated with the development of PH, therefore genetic background risk factors for the development of PH in SCD are likely to play a role. The current study will be one of the largest cohorts of SCD patients where cardiovascular phenotype is extensively characterized. The  $\beta^S$  mutation occurs on at least five different haplotypes defined by the presence of restriction sites within the 50 kilobase  $\beta$ -globin gene cluster which includes a region of high recombination immediately 5' to HBB on chromosome 11. These  $\beta^S$  haplotypes may be associated with differences in SCD severity and phenotypic expressions including PH. A more refined understanding of the haplotype differences flanking the sickle mutation would therefore be helpful in parallel with searches for other genetic modifiers in SCD related PH. As such, in this study patients consenting to participate in the genetic portion of this study will undergo an extensive genome wide genetic analysis followed by segments of regions associated with PH. When available in the next five years, whole genome sequence DNA on this population samples will be performed. Specifically, automated DNA sequencing of candidate genes, novel PCR based assays, and “chip” based high-throughput SNP detection platforms will be conducted at the NHLBI through the Division of Intramural Research or through collaboration with other Institutes.

We will be particularly interested in evaluating a number of potential genetic risk factors for PH in individuals with SCD. Example of genes of interest are included in redox, inflammatory, cell adhesion, endothelial function, vasoregulation, vascular proliferation, cell cycle regulation pathways, as well as genes related to red blood cell function and structure and globin regulators.

## **3 STUDY OBJECTIVES AND PURPOSE**

Our study has the following major objectives:

1. Screening to identify patients with sickle cell disease who have pulmonary hypertension and to create a cohort with an established cardiovascular phenotype linked to a biomarker and DNA repository
2. In a randomized, double-blind, placebo-controlled phase II/III trial, to determine the safety and efficacy of 16 weeks of sildenafil therapy on exercise capacity (six-minute walk distance), echocardiographic estimates of right ventricular systolic pressure, and symptoms in patients with sickle cell disease and pulmonary hypertension, defined by TRV  $\geq 2.7$  m/s
3. Via a right heart catheterization in subjects with more severe pulmonary hypertension (TRV stratum), to evaluate and compare the acute hemodynamic effects of inhaled nitric oxide and of oral sildenafil at rest in the catheterization laboratory and to determine the changes in hemodynamics after 16 weeks of sildenafil therapy

4. To evaluate prospective clinical outcomes in the subjects participating in the Observational Follow-up Study
5. To provide subjects with open-label sildenafil for up to one year after completion of the Main Interventional Trial and to evaluate the long term safety of sildenafil in this population

The primary endpoint in the Main Interventional Trial is change in six minute walk distance across the 16 week double-blind phase.

## **4 STUDY DESIGN AND METHODS**

### **4.1 Overview**

Up to 1000 subjects will be screened based on medical history, physical examination, laboratory testing, transthoracic Doppler-echocardiography, and 6MW test. All consented subjects in this cohort will provide plasma and serum for storage and measurement of BNP and DNA for a repository.

Patients found to have a screening TRV of  $\geq 2.7$  m/s and 6MW distance between 150 and 500 meters and who satisfy all inclusion/exclusion criteria will be enrolled in the 16 week, randomized, double-blind, placebo-controlled trial of sildenafil versus placebo. During the MIT baseline period, among other things, an additional echocardiogram and 6MW will be conducted. Subjects whose additional baseline evaluations satisfy the randomization criteria will be randomized to the MIT; 132 subjects will be randomized in all. Subjects will be stratified and randomized based on site and TRV stratum.

One-half of the subjects, those with TRV  $\geq 3.0$  m/s, will also be evaluated with right heart catheterization (RHC) before and after 16 weeks of the intervention. Study assessments will occur at weeks 6, 10, and 16 or early withdrawal. The primary endpoint is change in 6MW distance across this study phase. Secondary endpoints include non-invasive estimation of pulmonary artery systolic pressure by transthoracic Doppler-echocardiography, plasma NT-BNP levels, cardiovascular and sickle cell related symptoms and events, and quality of life scores.

Screened subjects will proceed into the Observational Follow-up Study at the point in which they either are not qualified to participate in the MIT or complete/discontinue participation in the MIT/Open-label Follow-up Phase. Subjects may be contacted every 6-12 months for up to 3 years to assess major disease-related complications, including mortality; subject follow-up during this study will be at the discretion of each clinical site.

Recruitment into the Screening Phase and MIT is expected to extend for approximately 13 months. Subjects who complete the double-blind phase will be eligible to participate in the Open-label Follow-up Phase and will be treated with sildenafil for up to 1 additional year; only AE data will be collected during this period. Subjects in the Observational Follow-up Study will continue through the end of their third study year (counting from date of signature on the Screening Informed Consent).

**Figure 2. walk-PHaSST Study Design**[figure not shown]

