##### **Open-label Follow-up Phase of Main Interventional Trial**

Completion of Main Interventional Trial.

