## 1                   PRECIS

Sickle cell disease (SCD) is an autosomal recessive disorder and the most common genetic disease affecting African-Americans. Approximately 0.15% of African-Americans are homozygous for sickle cell disease, and 8% have sickle cell trait. Acute pain crisis, acute chest syndrome (ACS), and pulmonary hypertension are common complications of sickle cell anemia. Pulmonary hypertension (PH) has now been identified as a marker of mortality in adults with sickle cell disease. Sildenafil has been proven beneficial in pulmonary hypertension (PH) and recent phase I/II studies from the intramural National Institutes of Health (NIH) suggest it is well tolerated and efficacious in the SCD population. Furthermore, a number of recent studies have suggested that nitric oxide (NO) based therapies may have a favorable impact on sickle red cells at the molecular level and could improve the abnormal microvascular perfusion that is characteristic of sickle cell anemia.

The project has 3 distinct components:

1.    **Screening Phase.** Approximately 1000 subjects with sickle cell disease will be screened. Assessments will include historical and laboratory data, Doppler echocardiogram, 6-minute walk test, plasma/serum, and DNA for banking.
2.    **Main Interventional Trial.** The randomized, double-blind, placebo controlled phase is designed to determine the effects of 16 weeks of sildenafil therapy on exercise endurance, cardiopulmonary hemodynamic parameters and symptoms in this patient population. The Open-label Follow-up Phase is designed to provide up to 1 additional year of sildenafil therapy to subjects who completed the randomized, double-blind phase.
3.    **Observational Follow-up Study.** All patients who sign informed consent for the Screening Phase are also consenting to participate in the Observational Follow-up Study. Screened subjects will proceed into the Observational Follow-up Study if a) they do not qualify for -or choose not to participate in the MIT; b) are discontinued for any reason during the MIT or the Open-label Follow-up Phase; or c) complete the Open-label Follow-up Phase. Subjects may be contacted every 6-12 months for up to 3 years to assess major disease-related complications, including mortality; subject follow-up during this study will be at the discretion of each clinical site.

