| Echocardiogram (LV systolic/diastolic function)                                                                                                                                                                                                            | X  | X                              |                | X                   |                                         |
| Right heart catheterization – Hemodynamic parameters at rest                                                                                                                                                                                   | X              |                                |                | X                   |                                         |
| 6-minute walk test                                                                                                                                                                                                                                         | X  | X                              | X              | X                   |                                         |
| Borg dyspnea index                                                                                                                                                                                                                                         | X              | X                              | X              | X                   |                                         |
| NYHA/WHO functional class assessment                                                                                                                                                                                                                       | X              | X                              | X              | X                   |                                         |
| Pregnancy test                                                                                                                                                                                                                                             | X              | X                              | X              | X                   |                                         |

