### 9.3.2 Clinical Laboratory Tests

Clinical laboratory tests (including the pregnancy test, if applicable) will be performed on blood samples collected at screening and all clinic visits for the Main Interventional Trial. Urinalysis laboratory tests will be performed on urine samples collected at screening and all clinic visits for the MIT as well. The following laboratory tests will be performed:

- Liver function tests (AST, ALT, albumin, total protein, total bilirubin, alkaline phosphatase)
- Renal function tests (potassium, sodium, chloride, bicarbonate, blood urea nitrogen (BUN), and creatinine)
- Mineral panel tests (magnesium, phosphate, calcium)
- CBC (Hemoglobin, hematocrit, RBC, MCHC, mean cell volume (MCV), reticulocyte counts, white blood cell (WBC) count, platelet count, and ANC)
- LDH
- INR values for subjects who are on vitamin K antagonists (e.g. warfarin)
- Activated Partial Thromboplastin Time (aPTT) for subjects who are on therapeutic doses of unfractionated heparin

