### 13.9 Pregnancy Reporting

Because of potential adverse effects on the fetus, pregnant subjects will be excluded from the study. Female subjects who are pubertal will be regularly assessed throughout the study. In the event of a positive pregnancy test, the subject will be immediately informed of this result and will have sildenafil treatment discontinued.

The investigator, or his/her designee, will collect pregnancy information on any female who becomes pregnant while participating in this study. The investigator or his/her designee will record pregnancy information on the appropriate form and submit it to the DCC Product Safety Associate within 2 weeks of learning of a subject’s pregnancy. The

subject will also be followed to determine the outcome of the pregnancy. Information on the status of the mother and child will also be reported to the DCC. Generally follow-up will be no longer than 6 to 8 weeks following the estimated delivery date. Any premature termination of the pregnancy will be reported.

While pregnancy itself is not considered to be an AE or SAE, any pregnancy complication, elective termination of a pregnancy for medical reasons, or spontaneous abortion will be recorded as an AE or a SAE, as appropriate.

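### Table 4 and section 4.1 schedule no pregnancy test during up to a year of open-label sildenafil, in conflict with sections 13.9, 7.1 and, on one reading, 9.3.2

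*Protocol*

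**What the plan says.** **Schedule.** In Protocol Table 4 the row "Pregnancy test" is marked at baseline and at weeks 6, 10 and 16. Its open-label cell is empty, and the only row with an open-label mark is adverse events. Section 4.1 says of the open-label year that "only AE data will be collected during this period". Section 4.4.4 adds dosing schedules to what is collected and has sites follow patients every 1-3 months. It does not mention a pregnancy test.

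**Pregnancy rules.** Section 13.9 gives the reason: "Because of potential adverse effects on the fetus, pregnant subjects will be excluded from the study". It continues: "Female subjects who are pubertal will be regularly assessed throughout the study", and then: "In the event of a positive pregnancy test, the subject will be immediately informed of this result and will have sildenafil treatment discontinued". Section 7.1 lists a positive blood HCG or pregnancy among the reasons to stop therapy.

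**Laboratory rule.** Section 9.3.2 reads, in part, "including the pregnancy test, if applicable) will be performed on blood samples collected at screening and all clinic visits for the Main Interventional Trial".

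**Where the open-label phase belongs.** The Synopsis has the heading "Open-label Follow-up Phase of Main Interventional Trial". The Precis describes the phase within its Main Interventional Trial component ("The Open-label Follow-up Phase is designed to provide up to 1 additional year of sildenafil therapy"). Section 7.1 also calls it a phase of that trial, and section 4.4.4 is numbered under it. Objective 5 in section 3 instead places open-label treatment after the trial is completed.

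**The concern.** The protocol treats pregnancy as a reason to stop sildenafil because of possible harm to the fetus. The stopping rule in 13.9 is triggered by a test result, so it works only if a test is done. Coordinators normally plan visits from the schedule table, and here the table and the overview agree that the open-label phase has no pregnancy test. A site that follows them would learn of a pregnancy only if the subject reported it or it became clinically evident, and exposure would continue until then. This phase is the longest period of dosing, and for former placebo subjects it is their first chronic exposure to the drug.

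The adverse event query at each contact is not a substitute. Section 13.9 does not regard a pregnancy as an AE or SAE in its own right; only complications, losses and medically indicated terminations are recorded that way. An uncomplicated pregnancy could therefore pass through AE-only collection unrecorded. The same section asks sites to collect pregnancy information on any female who becomes pregnant while participating, and this too does not fit a phase that collects only AE data.

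**Working it through.** The plan states no figure to reproduce. The check compares the sections and then counts weeks.

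**1. Is the blank cell real?** A lost mark in a converted table is possible, but 4.1 says the same in prose, and the adverse events row of the same table does carry an open-label mark. The blank is what the protocol says.

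**2. Can the sections be reconciled?**

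| Reading | 9.3.2 | 13.9 | Table 4 and 4.1 |
|---|---|---|---|
| Open label is part of the main trial (Synopsis, Precis, 4.4.4, 7.1) | Test at every open-label clinic visit | Regular assessment applies | No test: at odds with both |
| Open label follows the main trial (section 3, objective 5) | Does not reach open label | Regular assessment still applies, as the subject is in the study and on drug | No test: at odds with 13.9 |

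Neither reading brings all the sections into line.

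**3. How long is the gap?** Inputs: double-blind phase 16 weeks; open label up to 1 year, taken as 52 weeks; contacts every 1-3 months (Synopsis, 4.4.4, 13.1).

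- Double-blind phase: 4 tests (baseline, weeks 6, 10, 16). Nominal gaps: 6 - 0 = 6, 10 - 6 = 4 and 16 - 10 = 6 weeks, so the longest is 6 weeks.
- Open label by Table 4: 0 tests in up to 52 weeks. The week 16 test covers entry to the phase only.
- Randomized to sildenafil: total time on drug 16 + 52 = 68 weeks; share with no scheduled test 52/68 = 76%.
- Randomized to placebo: chronic sildenafil time is the open-label phase alone, so 52/52 = 100%.

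**4. What would testing at the planned contacts give?** Between 12/3 = 4 and 12/1 = 12 tests per subject in the year, at intervals between 52/12 = 4.3 weeks and 52/4 = 13 weeks.

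**The case against.** The strongest reply is that Table 4 is not a complete list of open-label procedures. Its symptoms row, which includes priapism, is also blank for open label, yet 4.4.2.3 requires males to be monitored in the clinic after their first open-label dose. Dosing schedules are collected under 4.4.4 with no mark in the table. Section 4.1 describes data collected and does not forbid a test, and 9.3.2 may already require one. This stands. A reader might infer that the protocol deliberately withdraws pregnancy surveillance in open label; the text does not support that. It shows a schedule that was not aligned with the rules elsewhere.

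It is also fair that 13.9 names neither a test nor a frequency, and that its reference to the whole study cannot be literal: the Observational Follow-up Study has no pregnancy test in Table 3. But that component gives no study drug, whereas open label does. The sentence stands under Pregnancy Reporting, and the next one acts on a positive test. The wording is loose, but a phase on sildenafil with no scheduled test still does not fit it.

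Entry requires reliable birth control or inability to bear children (5.3.1). That lowers the chance of pregnancy but does not detect one. The Synopsis criterion for open label is completion of the main trial, with no stated re-check of contraception.

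A reader might go further and infer that open-label dose increases go unsupervised, since doses rise every two weeks while AE contacts come every 1-3 months. The documents do not support this as a defect. Titration is conditional on tolerance, 4.4.4 points to the rules in 7.2, earlier contact is not barred, and the manual of operations, which is not shown, may add contacts.

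**Conclusion.** The point holds as a conflict within the protocol that bears on subject safety. Table 4 and 4.1 disagree with 13.9 and leave the pregnancy criterion in 7.1 without a scheduled means of detection. They also disagree with 9.3.2 if open label is part of the main trial, as most of the text has it. For a site that follows the schedule, the size is up to 52 weeks with no planned test: 76% of time on sildenafil in the active arm and 100% of chronic sildenafil time in the former placebo arm.

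This assumes a full open-label year and a site that does not read 9.3.2 as covering open label. A site that does would already test at its clinic visits. The number of women affected cannot be given: the protocol states no sex split, open label is optional, and dropout is given only as up to 10%. The conflict does not depend on that number. The efficacy analyses are not affected. The correction should be made, because it carries out the protocol's own rule at little cost.

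**What to change.** Mark the pregnancy test in the open-label column of Table 4, at the contacts already planned every 1-3 months, for females able to bear children. Amend 4.1 so that open-label collection covers AE data, dosing schedules and pregnancy tests; it then agrees with 4.4.4, 9.3.2 and 13.9. Dose steps and the 1-3 month interval stay as they are.

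The cost is one amendment to two places and about 4-12 routine tests per such subject over the year. Where a site makes contact remotely, a clinic visit or a home test kit is needed as well. The endpoint, dosing and sample size do not change.
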